#### Withdrawals

Subjects who meet any of the criteria shown in Table 3 will be withdrawn from the study. Reasons for withdrawal will be recorded in a case report form (CRF), and the patient(s)’ data will be analyzed using the intention-to-treat (ITT) method.

**Table 3 Tab3:** Withdrawal criteria for the *Onkyeong-tang* (OKT) clinical trial

Withdrawal criteria	
1. Those whose compliance is less than 70%	
2. Those who become pregnant during the trial period	
3. Those who need surgery or hospitalization due to accidents or other diseases	
4. Patient withdrawal of consent	
5. Those who have used forbidden medicines or treatments such as anticoagulants, psychotropic drugs, or other medications or treatments that may have effects on the symptoms of CHF	
6. Those who need standard treatment because of the aggravation of CHF symptoms	
7. Occurrence of SAEs	
8. Occurrence of other inevitable situations that may make it difficult to continue the trial process 9. Principal investigator’s (PI’s) judgement to discontinue the trial due to some factors affecting the study results	

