### Compliance calculation

The participants will be provided with a total of 93 investigational medications at visits 2 and 3. Compliance calculation will be conducted at visits 3 and 4. The formula for calculating medication compliance is as follows:

Compliance (%) = (93 – remaining drugs/expected intake) × 100.

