#### Efficacy

For the efficacy assessment, ITT analysis, a method for including all randomly assigned patients in the analysis regardless of violation or dropout, will mainly be used. Per-protocol (PP) analysis, a method which excludes subjects who do not comply with the study protocol or who have missing data, will also be implemented. The missing values of the efficacy assessment variables will be analyzed using the last-observation-carried-forward (LOCF) method.

A paired *t* test will be used for within-group analysis of the primary and secondary outcome variables. Between-group analysis will be performed using repeated measures ANOVA and the paired *t* test for the primary outcome variable. To measure secondary outcome variables, mean changes in the CHH VAS score, the BT, and the results of the WHOQOL-BREF and CST will be assessed. Repeated measures ANOVA and paired *t* tests will be carried out for the CHH VAS score. A repeated measures ANOVA will also be performed for BT. ANOVA and post hoc analyses will be performed for the WHOQOL-BREF results, and a paired *t* test will be used for the CST results. For the analysis of the Questionnaire of Pattern Identification, ANOVA and post hoc tests will be performed, and for the Questionnaire of Cold Hypersensitivity, Cronbach’s alpha and a correlation analysis will be performed.

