However, this study has a few limitations. First, a few participants in this trial are likely to be able to distinguish subtle differences between the placebo and test drugs, because they may have been a participant in similar clinical trials at the recruiting hospital. Second, because CHHF is a disease that is easily affected by cold weather, it is possible that changes in weather may have an influence on the outcomes. Therefore, although the BT measurement and the CST are performed after a relaxation period of 20 min at 24 ± 1 °C in the examination room, warmer weather is likely to produce better results, and colder weather may negatively affect the results. Furthermore, we could not fully exclude other underlying diseases that cause CHHF, because laboratory tests such as the antinuclear antibody (ANA) test could not be performed due to the small size of our research grant. Additionally, because the pathogenesis of CHHF is not clear, all of the CHHF-related diseases are not fully known. Finally, this study sets the criteria for dropout, which may affect the results of this study. For example, those who have used medications or treatments that may have effects on the symptoms of CHF, such as anticoagulants and psychotropic drugs, will be withdrawn. Nevertheless, those who take other medications may have taken them because OKT had not improved their symptoms. As such, when we drop out the subjects with low therapeutic effect, it may influence the results of the study. Nevertheless, efficacy data will be analyzed based on the ITT analysis; therefore, dropout is very unlikely to translate into better results, and in general, the more dropouts, the lower the cure rate. Among the forbidden drugs, anticoagulants were contraindicated, because the body temperature can be increased due to the blood flow-improving effects of anticoagulants. Drugs for hyperthyroidism and antipyretic analgesics were prohibited because they can affect the body’s heat metabolism. Psychotropic drugs were prohibited because they may cause problems related to research ethics. In addition, those whose compliance is less than 70% will be withdrawn. During the clinical trial period, compliance should be monitored to guarantee the power of the study. Compliance data are helpful for the interpretation of trial results to avoid erroneous conclusions and to enrich the value of the results [23]. High levels of non-compliance in a clinical trial may provoke the risk of a type II error (also called beta error or manufacturer’s risk). This is the risk of finding no meaningful difference in drug action between the test drug and control when there is a real difference. Increasing the sample size can reduce this risk; however, it will induce an increase of the expense in trial cost [24]. If the compliance is less than 70%, the effect of the OKT formulation can be lowered, and the result of the study may not be accurate; therefore, those with low compliance will be withdrawn. Poor compliance was also suggested as a dropout criterion in other clinical trials studying PURIAM110 (a dietary supplement) [25], Korean red ginseng [26], and Taeumjowi-tang (a traditional Korean medicinal extract) [27], among others. Other requirements are also proposed as dropout criteria because they may affect ethical issues or research accuracy. Although these criteria may have some impact on the outcome of the study, they were presented to comply with research ethics and to verify the effect of the research medication itself.

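### Response-related withdrawal from the study replaces week-8 VAS with carried-forward values, and the ITT label does not make that safe

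*Protocol article*

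**What the plan says.** Under Withdrawals: "Subjects who meet any of the criteria shown in Table 3 will be withdrawn from the study". The object is the study, not the study medication. Three criteria in Table 3 matter here:

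- Criterion 1: "Those whose compliance is less than 70" per cent.
- Criterion 5: forbidden medicines, including "other medications or treatments that may have effects on the symptoms of CHF".
- Criterion 6: "Those who need standard treatment because of the aggravation of CHF symptoms".

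The same section says that withdrawn patients' data are analysed by ITT. The Efficacy section describes ITT as "a method for including all randomly assigned patients in the analysis regardless of violation or dropout", makes it the main analysis, and fills missing efficacy values by LOCF. The Sample size calculation section defines the effect as the between-group difference in mean VAS change 8 weeks after randomisation, within 3 days.

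The Discussion accepts that some participants may turn to other medicines because OKT has not helped them, and that dropping low responders may influence the results. It then concludes that "efficacy data will be analyzed based on the ITT analysis; therefore, dropout is very unlikely to translate into better results".

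**The concern.** Worsening CHF is deterioration of the primary symptom itself. The Discussion links use of other medicines to lack of effect, and poor compliance can follow from it too. If OKT works, or if it is poorly tolerated, these events may occur at different rates in the two arms.

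A participant withdrawn on one of these grounds before visit 4 contributes no week-8 VAS. The analysis then uses the visit-3 score, or the baseline score if withdrawal comes before visit 3. Including everyone under an ITT heading does not restore an outcome that was not measured. At stake is whether the main comparison, on a subjective scale, reflects the 8-week state of everyone randomised. The Discussion tells readers that any distortion will be conservative, and that does not follow.

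**Working it through.** **How many participants.** The Sample size calculation section gives 56 per arm with 20% dropout. 56 × 0.8 = 44.8, so the plan expects about 45 per arm to complete. The number before inflation cannot be reproduced, because the article does not give the effect size, SD or power. Over both arms, 112 × 0.20 = 22.4, or about 22 participants. The 20% is not split by reason, so 22 is an upper limit for this rule at the planned rate.

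**Direction of the bias.** Let w be the share of an arm withdrawn before visit 4. Let b be the mean carried-forward change minus the true week-8 change among those withdrawn. Then

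bias in (OKT − placebo) = w_OKT × b_OKT − w_placebo × b_placebo.

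A negative bias favours OKT, since a fall in VAS is improvement. The bias is zero when the two products match, and nothing in ITT makes them match. With 10% withdrawn on OKT and 30% on placebo, and the same b in both arms:

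- b = +1: 0.10 − 0.30 = −0.2 (favours OKT)
- b = +2: 0.20 − 0.60 = −0.4 (favours OKT)
- b = −1 or −2: +0.2 or +0.4 (favours placebo)

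**Illustration with no drug effect.** All inputs are assumptions: SD of change 2; correlation 0.6 between week-4 and week-8 change; mean improvement 0.75 at week 4 and 1.5 at week 8 in both arms; in each arm, the participants with the worst week-4 change withdrawn after visit 3; 56 per arm.

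With m the mean of the worst fraction w of a standard normal variable,

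b = (−0.75 + 2m) − (−1.5 + 0.6 × 2m) = 0.75 + 0.8m.

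- w = 0.10: m = 1.755, b = 2.154, w × b = 0.215
- w = 0.30: m = 1.159, b = 1.677, w × b = 0.503

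Bias at 10% OKT and 30% placebo: 0.215 − 0.503 = −0.29.

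A simulation of 4,000 trials per scenario, tested with an independent-samples t test, agrees:

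| Withdrawn, OKT / placebo | LOCF bias (VAS points) | p < 0.05, LOCF | p < 0.05, full follow-up |
|---|---|---|---|
| 20% / 20% | 0.00 | 2.0% | 4.5% |
| 15% / 25% | −0.16 | 3.4% | 4.3% |
| 10% / 30% | −0.29 | 6.5% | 5.0% |
| 30% / 10% | +0.28 | 6.7% | 5.5% |

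With week-8 VAS observed for everyone, the bias was within 0.01 of zero in every row.

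**Against the Discussion.** The Discussion adds that more dropouts generally mean a lower cure rate. That would be a reasonable argument if dropouts were scored as failures. Here the endpoint is a mean change and the missing value is an earlier score. Even when the carried-forward score is pessimistic (b > 0), it penalises whichever arm loses more people. If that arm is placebo, OKT looks better.

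**The case against.** The authors disclose the issue as a limitation, the trial is called a pilot, and the article condenses protocol version 2.1, which might provide for visits after withdrawal. That tempers the point without removing it. The text shown states withdrawal from the study, the Discussion treats these people as dropouts, and the disclosure ends in an argument that fails.

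Several stronger readings are tempting, and the documents do not support them:

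- *The ITT analysis cannot be done.* It can: all randomised participants with LOCF is a computable analysis. What it lacks is an observed week-8 outcome for those withdrawn early.
- *A VAS measured at visit 4 is thrown away when compliance proves low.* A reader might infer this because "Compliance calculation will be conducted at visits 3 and 4" and Table 4 schedules VAS at visit 4 as well. No text discards a measured value, and LOCF applies only to missing ones. The loss concerns withdrawals before visit 4.
- *The rule costs 22 outcomes.* The 20% may also cover withdrawal of consent, loss to follow-up, and dropout after visit 4, which costs no week-8 value.
- *The standard error rises because only about 90 of 112 are observed.* The factor √0.8 = 0.894, an 11% difference, describes a completers-only analysis. Under LOCF all 112 enter.
- *Criterion 9 is outcome-dependent.* The investigator's "judgement to discontinue the trial due to some factors affecting the study results" is vague, but the text does not tie those factors to response.
- *A bias of 0.3 points is to be expected.* It needs a threefold imbalance in withdrawal that the documents give no reason to predict. At equal withdrawal and equal carry-forward error the bias is zero.

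**Conclusion.** The point holds in limited form. Withdrawal from the study under criteria 1, 5 and 6 can be related to response. For participants withdrawn before visit 4, LOCF replaces the week-8 VAS, so the main analysis does not estimate the 8-week change in all randomised participants. The Discussion's claim that ITT makes dropout conservative is incorrect for this endpoint and this imputation.

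The size is uncertain. At most about 22 of 112 participants are affected at the planned dropout rate. The bias is about zero if withdrawal and carry-forward error are alike in the two arms. Under the assumed inputs it is about 0.16 VAS points at 15% versus 25% and about 0.3 at 10% versus 30%, in either direction, with only a small rise in false positives in that last case. The SD, correlation, improvement and imbalance are assumptions, not figures from the article. The conclusion that the bias has no guaranteed direction does not depend on them. This bias arises through LOCF, so it should not be counted again in any separate criticism of LOCF.

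**What to change.** 1. In Withdrawals, separate stopping study drug from leaving the study. Decisions on study drug and clinical care stay as they are.
2. Participants who meet a Table 3 criterion, other than withdrawal of consent, continue the scheduled visits for VAS where still possible. All collected VAS values enter the ITT analysis.
3. State that a VAS measured at visit 4 is used whatever the visit-4 compliance result, and that this result serves only to define the per-protocol set.
4. Delete the reassurance in the Discussion, or replace it with a statement that dropout combined with LOCF can favour either arm.

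The cost is small: Table 4 already schedules VAS at visits 3 to 5, so the extra burden is a few visits by participants no longer on drug. The estimate will include the effect of any other treatment taken, and the report should say so. Timing limits the gain. Recruitment began on 28 May 2018 and was due to finish in May 2020, the month of publication, so continued follow-up helps only participants still within their 12 weeks. Visits already missed cannot be recovered. Items 3 and 4, and the use of every value already collected, remain possible for the whole trial before unblinding.

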### Procedure

#### Recruitment

A total of 112 subjects who meet the inclusion criteria will be competitively recruited through three Korean medicine university hospitals located in three cities in Korea. The Korean Medical Hospital of Sangji University will recruit 32 subjects, Semyung University Korean Medical Hospital at Chungju will recruit 40 subjects, and Semyung University Korean Medical Hospital at Jecheon will recruit 40 subjects. Each institute will recruit subjects through public outdoor advertisements using posters and other means. Those who are interested in participating in the clinical trial will be invited to contact the CRC or PI to obtain detailed information about the clinical trial and to schedule a screening visit.

#### Study schedule

The items to be checked at each patient visit are shown in Table 4.

**Table 4 Tab4:** Study schedule for the *Onkyeong-tang* (OKT) clinical trial

	Screening	Treatment period			Follow-up
	Visit 1 (day − 7 through − 2)	Visit 2 (day 0)	Visit 3 (day 28 ± 3)	Visit 4 (day 56 ± 3)	Visit 5 (day 84 ± 3)
Informed consent	●				
Eligibility criteria	●				
Randomization		●			
Medication compliance			●	●	
Vital signs	●	●	●	●	●
Body measurements^a^	●	●	●	●	●
Collection of demographic, sociological,^b^ and gynecological information	●				
Medical history	●	●	●	●	●
General physical examination	●	●	●	●	●
Thermometer measurement^c^	●	●	●	●	●
VAS	●	●	●	●	●
Monitoring of AE			●	●	●
Questionnaire of Pattern Identification	●				
Questionnaire of Cold Hypersensitivity		●			
Cold stress test		●		●	
WHOQOL-BREF		●		●	
Laboratory tests^d^	●			●	
Chest X-ray & ECG	●				
Medication		●	●		
Test of blindness				●	

^a^ Height, weight, and BMI, but only weight for visits 2, 3, 4, and 5

^b^ Age, occupation, digestion, exercise, smoking, drinking, sleep, etc.

^c^ Thermometer measurement of ST32, LR3, PC8, and LU4 at every visit

^d^ Screening: Hematological examination (WBCs, RBCs, Hb, platelets), blood chemistry test (BUN, Cr, AST, ALT, r-GTP, glucose), thyroid function test (free T4, TSH), urine test, pregnancy test (urine hCG)

Visit 4: Hematological examination (WBCs, RBCs, Hb, platelets), blood chemistry test (BUN, Cr, AST, ALT, r-GTP)

Abbreviations: *AE* adverse event, *ALT* alanine aminotransferase, *AST* aspartate aminotransferase, *BMI* body mass index, *BUN* blood urea nitrogen, *Cr* creatinine, *ECG* electrocardiogram, *r-GTP* gamma-glutamyl transpeptidase, *Hb* hemoglobin, *hCG* human chorionic gonadotropin, *RBC* red blood cell, *TSH* thyroid-stimulating hormone, *VAS* Visual Analog scale, *WBC* white blood cell, *WHOQOL-BREF* World Health Organization Quality of Life Scale-abbreviated version

### Interventions

After enrollment, the participants will receive 3 g of OKT or placebo three times a day for 8 weeks. Each group will take the designated medicine with warm water before or between meals.

The OKT and placebo will be supplied by Hanpoong Pharm & Foods Co. Ltd, Jeonju, Republic of Korea. We will be using OKT granulated extract which is composed of 1 g of *Evodiae Fructus*, 0.67 g of *Ginseng Radix Alba*, 0.67 g of *Paeoniae Radix*, 0.67 g of *Asini Corii Colla*, 0.67 g of *Cnidii Rhizoma*, 1.67 g of *Pinelliae Tuber*, 0.67 g of *Moutan Cortex Radicis*, 3.33 g of *Liriopis Tuber*, 1 g of *Angellicae Gigantis Radix*, 0.33 g of *Zingiberis Rhizoma*, and 0.67 g of *Glyzzirizae Radix*. These herbal medicines will be extracted and concentrated to 3 g per dose. The placebo granulated extract is composed of 1.7 g of lactose, 1 g of corn starch, 0.1 g of citric acid, 0.1 g of caramel coloring, and 0.1 g of *Ssanghwa* herbal flavor per dose. The placebo will appear identical to OKT in terms of color, shape, weight, flavor, and taste.

### Outcomes

The primary outcome will be changes in the CHF VAS score from baseline. Secondary outcomes will be the changes in VAS scores for cold hypersensitivity in the hands (CHH), changes in body skin temperature (BT) of the hands and feet, total score of the Korean version of the World Health Organization Quality of Life Scale-abbreviated version (WHOQOL-BREF), and the results of the cold stress test (CST).

#### Primary outcome variable

The primary outcome variable is VAS measurement of CHF symptoms. The VAS score is a 10-point scale representing no coldness as 0 and most severe coldness as 10. It will be used to evaluate the severity of CHF symptoms. The VAS will be measured at every visit, and the changes in score from baseline will be calculated.

#### Secondary outcome variables

##### VAS: measurement of CHH symptoms

The CHH VAS score will be used to assess the severity of symptoms. It will be measured at every visit, and the changes in score from baseline will be calculated.

##### BT: thermometer measurement

Participants will be asked to refrain from consuming caffeine, alcohol, and cigarettes; performing strenuous exercise; and taking hot showers at least 2 h prior to measurement. After a relaxation period of 20 min at 24 ± 1 °C in the examination room, the BT of both palms (PC8), anterior upper arms (LU4), center of the front thighs (ST32), and junctions of the first and second metatarsal bones (LR3) will be measured using a thermometer (Testo 835-T1; Testo, Lenzkirch, Germany) at every visit.

##### WHOQOL-BREF

The WHOQOL-BREF is a questionnaire used to assess quality of life based on 26 items. It consists of five domains: general quality of life, physical health, psychological health, social relationships, and environmental health. The Korean version of the WHOQOL-BREF developed by Min et al. [10] will be used to assess the quality of life of the patients with CHF symptoms at visits 2 and 4.

##### CST

The purpose of the CST is to measure the temperature recovery ability of both feet after cold stimulation. In this procedure, first the participants will rest for 20 min in a room set at 24 ± 1 °C to allow for stabilization to occur, and then the temperature of both feet will be measured. Next, participants will immerse both feet into a container filled with water at 20 °C for 30 s. Subsequently, their feet will be carefully dried with a towel, and the temperature of both feet will be measured immediately and then 6 min later. The temperature measurement point will remain the same for each foot. BT will be measured using an infrared thermometer (Testo 835-T1). The CST will be conducted at visits 2 and 4. The following is the recovery rate (RR) equation for the CST. The change in RR from baseline will be measured.
$$ \mathrm{RR}=\left({T}_6-{T}_0\right)/\left({T}_{base}-{T}_0\right)\times 100\%, $$

where:

*T*_6_ is the skin temperature 6 min after the CST

*T*_0_ is the skin temperature immediately after the CST

*T*_base_ is the skin temperature at baseline

### Questionnaire of Pattern Identification, Questionnaire of Cold Hypersensitivity

The Questionnaire of Pattern Identification will show the distribution of the pattern identification index in patients with CHF and will be performed at visit 1. The Questionnaire of Cold Hypersensitivity will be performed at visit 2.

### Safety assessment

To assess safety, vital sign measurement and a general physical examination will be performed at each visit. Renal and liver function tests (blood urea nitrogen [BUN], creatinine [Cr], aspartate aminotransferase [AST], alanine aminotransferase [ALT], and gamma-glutamyl transpeptidase [r-GTP]) and hematological examinations (white blood cells [WBCs], red blood cells [RBCs], hemoglobin [Hb], and platelets) will be conducted at visits 1 and 4. Confirmation of adverse events [AEs] will be performed at visits 3, 4, and 5.

### Compliance calculation

The participants will be provided with a total of 93 investigational medications at visits 2 and 3. Compliance calculation will be conducted at visits 3 and 4. The formula for calculating medication compliance is as follows:

Compliance (%) = (93 – remaining drugs/expected intake) × 100.

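### The printed compliance formula has a misplaced bracket: it returns about 9,160–9,300% at visits 3 and 4, so followed literally it can never trigger the below-70% withdrawal criterion

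*Protocol article*

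**What the plan says.** The Compliance calculation section of the protocol article states the supply, the timing and the formula:

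- Supply: "The participants will be provided with a total of 93 investigational medications at visits 2 and 3".
- Timing: "Compliance calculation will be conducted at visits 3 and 4".
- Formula: "Compliance (%) = (93 – remaining drugs/expected intake) × 100".

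Under Interventions, "the participants will receive 3 g of OKT or placebo three times a day for 8 weeks". Table 4 puts visit 3 at day 28 and visit 4 at day 56, each ± 3 days, and marks medication at both visit 2 and visit 3.

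The first withdrawal criterion in Table 3 is "Those whose compliance is less than 70" per cent. The Discussion repeats and defends that threshold. Under Efficacy, the per-protocol analysis is described as "a method which excludes subjects who do not comply with the study protocol or who have missing data", with no compliance percentage attached. Expected intake is not given a number, and no other part of the article prints the formula in a different form.

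**The concern.** A compliance percentage should be 0% when nothing is taken and 100% when the expected amount is taken. As printed, the formula subtracts a small ratio from 93 and multiplies the result by 100, so it lands in the thousands whatever the participant returns and barely distinguishes a full taker from someone who took nothing.

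The figure is not decorative. It is the measure behind a withdrawal criterion, and the Discussion justifies that criterion by appeal to study power and accuracy. If the expression were applied as written, no participant would be withdrawn for low compliance at a scheduled visit. The neighbouring sentence on supply is also loosely worded, and the formula depends on the 93 that it introduces.

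**Working it through.** **Inputs**

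- Units in the formula: 93 (Compliance calculation).
- Doses per day: 3 (Interventions).
- Visit 2 to visit 3: 25 to 31 days, nominally 28 (Table 4). Expected doses 75 to 93, nominally 84.
- Visit 3 to visit 4: 22 days (day 31 to day 53) to 34 days (day 25 to day 59). Expected doses 66 to 102, nominally 84.
- Threshold: below 70% (Table 3).
- Assumption: expected intake = 3 × days in the interval, since the article gives no number.

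The article contains no worked compliance value to reproduce.

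**Step 1. The formula as printed, (93 − remaining/expected) × 100, with expected = 84**

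- Nothing returned: (93 − 0/84) × 100 = 9,300%.
- All 84 doses taken, 9 returned: (93 − 9/84) × 100 = 9,289.3%.
- Nothing taken, 93 returned: (93 − 93/84) × 100 = 9,189.3%.

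**Step 2. What would bring the printed value below 70%?** This needs 93 − remaining/expected < 0.70, so remaining > 92.3 × expected. With 84 expected, that is 92.3 × 84 = 7,753.2 units.

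**Step 3. Across the visit windows**

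| Interval (days) | Expected doses | Printed, 0 left | Printed, 93 left | Units left needed for <70% |
|---|---|---|---|---|
| 22 | 66 | 9,300% | 9,159.1% | more than 6,091.8 |
| 25 | 75 | 9,300% | 9,176.0% | more than 6,922.5 |
| 28 | 84 | 9,300% | 9,189.3% | more than 7,753.2 |
| 31 | 93 | 9,300% | 9,200.0% | more than 8,583.9 |
| 34 | 102 | 9,300% | 9,208.8% | more than 9,414.6 |

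No possible return from 93 units comes near the threshold.

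**Step 4. The same terms with the bracket moved, (93 − remaining)/expected × 100, with expected = 84**

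- 0 left: 93/84 = 110.7%.
- 9 left: 84/84 = 100%.
- 34 left: 59/84 = 70.2%.
- 35 left: 58/84 = 69.0%.
- 93 left: 0%.

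The 70% threshold now separates participants, between 34 and 35 units returned.

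**Step 5. What the 93 is.** 31 days × 3 = 93, which is one 28-day interval plus its 3-day window. Eight weeks at three per day is 56 × 3 = 168. Two supplies of 93 give 186, enough for 62 days. The figures fit if 93 is supplied at each of the two visits, and do not fit if 93 is the supply for the whole trial.

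**The case against.** The strongest reply is that this is a typographical slip with an obvious meaning. The recovery-rate equation in the CST section brackets its numerator separately, so the intended pattern is easy to see. A result near 9,200% would be noticed at the first calculation. The article condenses a full protocol (version 2.1) that is not shown, so the working formula may be correct. All of this stands, and it is why the point is minor. It does not make the printed line right: the article chose to state the formula, and nothing else in it supplies a correct one.

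Four stronger readings are tempting, and the document does not support them:

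- *That 70% compliance could never be reached.* The reverse is true. On the printed formula everyone exceeds 70% at scheduled visits, and it is the below-70% criterion that cannot fire.
- *That the error decides the per-protocol set.* The Efficacy section gives no 70% cut-off. Any effect is indirect, through withdrawal, missing data or a judgement of non-compliance.
- *That 93 is the supply for all 8 weeks, so that even a corrected figure is capped at 93/168 = 55.4% and everyone fails.* Table 4 marks medication at both visits, compliance is calculated at two visits, and 93 is exactly 31 days' supply. The wording is loose, but that reading conflicts with the rest of the article.
- *That the trial's compliance data are wrong.* The article reports no compliance value and does not show which form was used.

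**Conclusion.** The point holds as a minor correction. Read with ordinary operator precedence, the printed formula gives about 9,160–9,300% at visits 3 and 4 (9,189–9,300% if expected intake is 84), so it can never trigger the below-70% withdrawal criterion there. The range rests on 3 doses per day, the Table 4 windows and at most 93 units returned.

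The restriction to scheduled visits matters little. After a very early stop with 3 expected doses, the printed value is still 6,200% to 6,300%, and it could fall below 70% only if expected intake were about one dose.

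The consequence for the efficacy results is limited. The main analysis is by intention to treat, includes all randomised participants and does not use the compliance figure. Withdrawal could reach it only through later missing values, which are carried forward, and only if the misprint had been applied in practice.

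**What to change.** 1. Print the formula as Compliance (%) = (93 − remaining drugs) / expected intake × 100, calculated separately for visit 2 to visit 3 and for visit 3 to visit 4.
2. State that expected intake is 3 × the number of days in the interval. A fixed 84 would misstate short intervals: a participant who took 58 of 66 expected doses over 22 days (87.9%) would score 58/84 = 69.0%.
3. Reconcile the supply sentence with Table 4 and with the 168 doses over 8 weeks. The figures fit only if 93 units are supplied at each of visits 2 and 3, and the sponsor should confirm this.
4. Check that the case report form or database uses the corrected form. If any value was derived from the printed one, recalculate it.

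The cost is one corrected line, one clarified sentence and a short data-management check. The dose, the 70% threshold, the sample size and the planned analyses are unchanged.
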